### Data management

Intention-to-treat analysis [51] with per protocol method is used in all the calculations. Per protocol method is chosen because of the nature of the acute condition, i.e. all patients are expected to get better. Descriptive statistics and appropriate multivariate analyses (Linear Mixed Models) will be used to decrease type I error in analyses of group differences over time. The Linear Mixed Models permit correlations (due to repeated measuring over time) between variables and can handle the missing values in a proper way.

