The new IT-based treatment (Internet/e-mail) regimen for acute WAD patients, emphases self-monitoring and skills training, as well as discussions led by a therapist. The patient will be instructed when to start and how to log onto the Internet treatment modules (seven modules; A – G), one at a time and get individualized support via e-mail from a therapist. The patient cannot log onto the next module if she/he has not completed the tasks in the previous module. Questions from the patients as well as answers from the therapist will be available on the treatment site, by consent from the patient, functioning as an additional support for the fellow patients, i.e. virtual group treatment.

#### Group 2

Face-to-face intervention involves groups of three to six patients led by therapists. The therapist meets with the group seven times during the acute phase following the accident. The face-to-face programme is planned to be similar to the IT-based treatment regimen described above, but differs in the way the treatment is administered. The programme consists of those seven treatment phases in seven modules described above (Additional file 1).

#### Group 3

Standard care of these patients currently involves a visit to a physical therapist, which provides a home exercise programme dealing with physical symptoms and advice of returning to normal activities as soon as possible. No further treatment is given except the home exercise programme that all patients get at the emergency ward (standard care) before randomisation.

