### Primary outcome

Primary outcome measure is disability measured with Pain Disability Index [39-41]. PDI is a 7-item inventory that is designed to measure interference with role-functioning due to persistent pain in the following areas: 1) family and home responsibilities, 2) recreation, 3) social activity, 4) occupation and education, 5) sexual behaviour, 6) self-care, and 7) life-support activity. Degree of interference is rated on 11-point numeric rating scales (NRS), ranging from 0 (no interference) to 10 (total interference). A total disability score range from 0 to 70. The PDI is found to be a reliable and valid measurement of disability in patients with persistent pain [39,41] as well as patients with acute pain [11]. A Swedish version of the PDI [25] is used in this project.

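### Data management names intention-to-treat and per protocol together as the one method for every analysis; the two are incompatible and the primary analysis set needs to be fixed

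*Protocol article*

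**What the plan says.** The Data management section of the protocol article sets the analysis population in two consecutive sentences: "Intention-to-treat analysis [51] with per protocol method is used in all the calculations", and then "Per protocol method is chosen because of the nature of the acute condition, i.e. all patients are expected to get better". It goes on to name linear mixed models for group differences over time and says that they "can handle the missing values in a proper way". The article defines neither population, does not rank them as primary and sensitivity, and gives no adherence threshold.

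The outcome affected first is the primary one: "Primary outcome measure is disability measured with Pain Disability Index". Because the rule covers every calculation, it also reaches the cost-utility analysis under Cost accounting analyses.

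The Intervention section shows what each arm has to adhere to:
- Group 1 works through seven Internet modules: "The patient cannot log onto the next module if she/he has not completed the tasks in the previous module".
- Group 2 attends meetings: "The therapist meets with the group seven times during the acute phase following the accident".
- Group 3 has no sessions after randomisation: "No further treatment is given except the home exercise programme that all patients get at the emergency ward (standard care) before randomisation".

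The Secondary outcome section adds an Exercise Diary that records compliance with the standard exercises.

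**The concern.** The two named sets answer different questions. One preserves the randomised comparison, and the other conditions on behaviour after randomisation. An analyst following the text could exclude non-adherers or keep them and claim in either case to have followed the plan, possibly after seeing the data. The primary comparison is therefore not fixed in advance.

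The stated reason does not help. Expected recovery in all arms may argue against carrying early, worse values forward. It does not argue for removing randomised patients.

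If exclusion did take place, it would not be neutral. In a condition where most patients recover, someone who recovers quickly has little reason to finish seven modules, and someone doing badly may give up. Removing either kind of patient shifts the mean of those who remain, in opposite directions. The mixed model offers no protection, because it deals with missing values among the patients in the analysis set and does not decide who belongs to that set.

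**Working it through.** **Text check.** The contradiction needs no arithmetic.

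1. Intention-to-treat: all randomised patients, in the arm allocated, whatever they completed.
2. Per protocol: a subset chosen by adherence after randomisation.
3. The two sets coincide only if nobody is excluded, in which case the per-protocol label has no content. If anyone is excluded, the analysis is no longer intention-to-treat.
4. The second sentence says that per protocol was chosen and gives a reason, so the phrase is not an obvious slip.
5. No other section defines or reconciles the two. Treatment fidelity (item 9) says only that the number of contacts is reported. The Intervention section locks modules in sequence but does not link completion to the analysis.

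**Possible size under literal exclusion.** The plan has no figure of its own to reproduce on this point. The only input from the article is 60 patients per group with two-sided alpha 0.05 (Study size and Power calculations). Whether 60 follows from the stated effect size is a separate matter that does not affect this point.

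Assumed inputs, not in the article:
- fraction *f* of an active arm excluded: 10%, 20% or 30%;
- gap *g* in mean Pain Disability Index (PDI) between excluded and retained patients, for prognostic reasons only: 0.3 or 0.5 SD;
- no true effect, no exclusions in the control arm, SD of 1, independent patients, and a single normal test of one active arm against control.

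With no true effect, the whole active arm has the control mean *m*. If the retained patients have mean *c*, then (1 − *f*)*c* + *f*(*c* + *g*) = *m*, so *c* = *m* − *fg*. Hence:

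- bias = *f* × *g*
- SE = √(1/60 + 1/[60(1 − *f*)])
- type I error = Φ(−1.96 + bias/SE) + Φ(−1.96 − bias/SE)

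| *f* | n retained v control | SE | *g* | bias (SD) | type I error |
|---|---|---|---|---|---|
| 0.10 | 54 v 60 | 0.188 | 0.3 | 0.03 | 5.3% |
| 0.10 | 54 v 60 | 0.188 | 0.5 | 0.05 | 5.8% |
| 0.20 | 48 v 60 | 0.194 | 0.3 | 0.06 | 6.1% |
| 0.20 | 48 v 60 | 0.194 | 0.5 | 0.10 | 8.1% |
| 0.30 | 42 v 60 | 0.201 | 0.3 | 0.09 | 7.3% |
| 0.30 | 42 v 60 | 0.201 | 0.5 | 0.15 | 11.6% |

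The sign follows the sign of *g*. If the excluded patients are doing worse, the active arm looks better than it is. If they are the early recoverers, it looks worse. The two-sided type I error is the same either way.

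The nearest figure in the article is the enrolment of about 200 against 3 × 60 = 180, which implies 1 − 180/200 = 10% drop-out. Drop-out is not non-completion, so this only shows that the low end of the range is plausible.

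**Asymmetry between arms.** If controls were also excluded, with fraction *f*₀ and gap *g*₀, the net bias would be *fg* − *f*₀*g*₀. The home exercises are common to all arms and are given before randomisation. The active arms could therefore fail on exercises and on modules or sessions, and the control arm on exercises only. That makes more exclusion in the active arms likely. It does not show that control exclusions would be zero, so the table is the one-sided case.

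**The case against.** The strongest reply is that the authors did not intend to exclude anyone. Their reason makes little sense as grounds for dropping non-adherers and good sense as grounds for not carrying early values forward in a recovering condition. The sentence about mixed models and missing values points the same way. On that reading the plan is to analyse observed data as allocated, and the fault lies in the terminology. The work cited for intention-to-treat may also define the approach, and it is not available here. This reading is credible and cannot be ruled out. But the text does not state it, and if it was meant, the wording still misdescribes the analysis.

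A second reply is that population definitions are often left to a full protocol or analysis plan. That would answer silence. Here the article is not silent: it fixes a rule that cannot be carried out as written.

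Three stronger readings are tempting but not supported:
- A reader might infer that patients who do not finish the modules will be excluded. No section ties module or session completion to the analysis.
- A reader might infer that exclusions would fall almost wholly on Groups 1 and 2. The Exercise Diary gives the control arm an adherence measure too, so only a probable imbalance can be claimed.
- A reader might take a type I error near 12% as a property of this trial. It comes from assumed inputs, and at 10% exclusion the error stays at 5.3-5.8%, close to nominal.

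**Conclusion.** The stated analysis set is wrong as written and must be corrected before the primary comparison can count as pre-specified. That conclusion rests on the text alone.

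The bias is conditional. It arises only if per protocol is applied literally, and its direction is unknown. On the assumed inputs it amounts to 0.03-0.15 SD in the PDI contrast, with a two-sided type I error of about 5.3-12% instead of 5%. The exclusion fraction, the prognosis gap and the absence of control exclusions are all assumptions; only the 60 per group and the alpha come from the article. The cost-utility contrast would be exposed to the same selection, but its size cannot be worked out from what is given.

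**What to change.** Replace the two sentences in Data management with wording to this effect:

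*The primary analysis includes all randomised patients in the arm to which they were allocated. It uses every available PDI value, regardless of modules or sessions completed, in the planned linear mixed model, and no values are carried forward. The cost-utility analysis uses the same set of patients. Any per-protocol analysis is a sensitivity analysis, with its adherence criteria for each arm fixed before the data are examined.*

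If the authors' purpose was only to avoid carrying values forward, this text achieves it.

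The cost is two sentences. Treatment, data collection and the sample size do not change. The estimated effect may come out smaller or larger than under per protocol, because the direction of any selection is not known.

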### Hypothesis

The main purpose of this study is to try a new behavioural medicine intervention strategy at acute phase aimed to reduce the number of patients who have persistent problems after the whiplash injury. The goal is also to identify which of three different interventions that is most cost-effective for patients with Whiplash Associated Disorders. In this study we are controlling for two factors. First, the effect of behavioural medicine approach is compared with standard care. Second, the manner in which the behavioural medicine treatment is administered, Internet or face-to-face, is evaluated in it's effectiveness and cost-effectiveness.

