### Study size and Power calculations for the sample

The power calculation is based on repeated three-group analysis. Since there are no previous studies to compare with, the power calculation is based on hypothetical reasoning of effects. Upon completion of treatment, all groups will be assumed to have achieved 75 per cent improvement in the main outcome variable, Pain Disability Index, compared with the baseline levels. We assume that at the one-year follow-up, standard-treatment group will have lost 75 percent of improvement and group 1 and 2 25 percent of improvement. This gives a long-term effect size which is >.80. At a significance level of .05, a two-tailed analysis requires 60 people in each group to attain a statistical power of .90. Time needed to include approximately 200 patients (including possible drop-outs) with these inclusion criteria is expected to take at least 1,5 to 2 years according to empirical experience.

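### Mixed models are credited with reducing type I error, which they do not do once arm contrasts are read at several visits, and PDI has no primary visit or contrast although the trial is sized on one year

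*Protocol article*

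**What the plan says.** Under Data management, the article states that "appropriate multivariate analyses (Linear Mixed Models) will be used to decrease type I error in analyses of group differences over time". The next sentence gives the reason: the models allow for correlation from repeated measurement and deal with missing values.

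Under Primary outcome: "Primary outcome measure is disability measured with Pain Disability Index". No visit and no group comparison is attached.

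Under Hypothesis, two comparisons are named. One is introduced with "First, the effect of behavioural medicine approach is compared with standard care"; the other is Internet versus face-to-face delivery. Study Design says that each programme is compared with standard treatment and that both short-term and long-term effects are evaluated, at 3, 6, 12 and 24 months. The caption of Figure 1 adds a measurement immediately after treatment, which makes five occasions after baseline.

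The section on study size says "The power calculation is based on repeated three-group analysis". It continues: "Upon completion of treatment, all groups will be assumed to have achieved 75 per cent improvement". At one year, standard care is assumed to have lost 75 per cent of the improvement and Groups 1 and 2 to have lost 25 per cent. Then: "This gives a long-term effect size which is >.80", and "At a significance level of .05, a two-tailed analysis requires 60 people in each group to attain a statistical power of .90". One year is the only time point singled out, but the section calls it neither the primary visit nor the primary test.

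**The concern.** The sentence on type I error is the only safeguard against false positives that the article offers, and it gives the model a property it lacks. Modelling the correlation makes each standard error right. It does not reduce the number of chances to declare an effect when three arms are compared at several visits.

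A single joint test of group differences over time would hold .05, but it cannot say which arm differs or when. The aims ask exactly that, so further contrasts will be read.

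The sections also do not meet. The trial is sized on a difference at one year, while the outcome section leaves the visit and the contrast open. A reader of the final report could not tell from this article whether the headline comparison was the one planned. If the gap were filled with a group effect averaged over all visits, the test would include an occasion at which the sponsor itself assumes no difference.

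**Working it through.** **Inputs from the article.** Two-sided alpha .05, power .90, 60 per group, standardised effect above .80 (taken as .80). Three arms. Four follow-up visits plus one post-treatment measurement. Three consecutive patients always allocated to the same arm. No standard deviation, baseline mean or between-visit correlation is given, so correlations below are assumptions shown as ranges.

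**The plan's own figure.** n per group = 2 × (1.960 + 1.282)² / 0.80² = 2 × 10.51 / 0.64 = 32.8, so 33 (34 with the t-test). A three-group analysis of variance with two arms equal needs 31. The stated 60 is not reproduced. With 60 per group, power at .80 is Φ(0.80 × √30 − 1.960) = Φ(2.42) = .99, and .90 power corresponds to an effect of 0.59. The article therefore has room for a stricter testing rule on its own effect size.

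**Error if contrasts are read separately at .05.** Simulation under no difference between any arms (200,000 replicates, equal correlation between visits):

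| Tests read | Family-wise error |
|---|---|
| One visit, the two comparisons in the Hypothesis section | .098 |
| One visit, three pairwise comparisons | .122 |
| Five visits, two stated comparisons, correlation .3 to .9 | .37 to .19 |
| Five visits, three pairwise, correlation .3 / .5 / .7 / .9 | .44 / .39 / .33 / .23 |
| Four follow-up visits, three pairwise, correlation .3 to .9 | .38 to .22 |
| One joint test over all visits | .05 |
| Pairwise visit tests read only after a significant joint test, correlation .3 to .9 | .05 to .03 |

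The last two rows show that a joint test does protect the error when no arm differs. That protection comes from testing once or gating on one test, not from the mixed model as such.

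**Dilution if visits are averaged.** As an illustration, assume the difference is zero at end of treatment (taken as month 2), rises linearly to 0.80 at 12 months and then stays there. The five differences are 0, 0.08, 0.32, 0.80 and 0.80, with mean 2.00 / 5 = 0.40. The variance of a five-visit mean is (1 + 4ρ)/5.
- ρ = .5: 0.40 / √0.60 = 0.516; power = Φ(0.516 × √30 − 1.960) = Φ(0.87) = .81.
- ρ = .7: 0.40 / √0.76 = 0.459; power = Φ(0.459 × √30 − 1.960) = Φ(0.55) = .71.

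The 12-month contrast alone has power .99 on the same assumptions.

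**Does the proposed primary contrast fit 60 per group?** Groups 1 and 2 together (120) versus Group 3 (60): standard error √(1/120 + 1/60) = 0.158 SD. The effect detectable at .90 is 3.242 × 0.158 = 0.51, against 0.59 for one pairwise contrast. With clusters of three the variance is multiplied by 1 + 2 × ICC. For an assumed ICC of .05 to .2 this is 1.1 to 1.4, and the detectable effect is 0.54 to 0.61, still below 0.80.

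**Does the sequence hold .05?** If all arms are equal, the gate is a true null and is passed 5 per cent of the time. If one programme equals standard care and the other does not, only one later null is true, and it is tested at .05. If the two programmes differ from standard care in opposite directions so that the pooled contrast is zero, only the gate can err.

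**The case against.** The best defence is that the sentence speaks of group differences over time, so it may mean that one longitudinal model replaces separate tests at each visit. The statement that power rests on a repeated three-group analysis fits this. On that reading the wording is loose, not wrong, and the joint test does hold .05. This stands as far as the joint test goes. It does not cover the contrasts that the aims need afterwards.

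A reader might infer that the plan commits the trial to some 15 unadjusted tests and that inflation is certain. The article does not support that. It names two comparisons under Hypothesis, lists four follow-ups, and takes the fifth occasion only from a figure caption. It nowhere says that each test is read at .05. Inflation is conditional.

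A reader might also infer that every visit is equally available as the primary one. The sizing assumptions point to one year with Groups 1 and 2 equal and better than standard care, so an intention is visible and needs only to be stated. Averaging over visits is likewise not stated; a group-by-time analysis could pick up the assumed divergence.

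Contrast coding and multiplicity detail may sit in a full protocol or an analysis plan not shown, so their absence alone is no fault. What remains is the stated claim about type I error and the mismatch between the sizing and the outcome section.

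Finally, the main purpose is "aimed to reduce the number of patients who have persistent problems after the whiplash injury", and one might ask for a proportion of patients with persistent disability as an outcome. The article gives no PDI cut-off for this, so no such outcome is proposed here.

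**Conclusion.** The point holds in a limited form. Mixed models are not a safeguard against multiple comparisons, and the primary outcome lacks the visit and contrast on which the trial is sized. The possible family-wise error is .10 to .12 at one visit and about .23 to .44 for three comparisons at five visits. Both figures apply only if contrasts are read separately at .05, and the second depends on an assumed correlation. The alternative of averaging over visits would cut power from .99 to about .81 to .71 under an assumed linear build-up of the effect and a correlation of .5 to .7. The error and dilution figures ignore clustering from allocation in threes. This should be corrected, but it does not threaten the feasibility of the trial.

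**What to change.** Delete the claim about type I error under Data management and put in its place:

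*The primary test is the 12-month PDI contrast of Groups 1 and 2 together versus Group 3, from the linear mixed model, two-sided .05, with baseline PDI as covariate and the allocation clusters of three accounted for. Only if this is significant are Group 1 versus Group 3 and Group 2 versus Group 3 each tested at .05. Internet versus face-to-face, all other visits and all other outcomes are secondary.*

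Add the 12-month visit to the Primary outcome section, so that it agrees with the section on study size.

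Cost: one paragraph. No new data or patients are needed, because baseline PDI is already collected before randomisation. The baseline covariate lowers the variance of the 12-month contrast by the square of its correlation with the outcome: 9 to 25 per cent at an assumed .3 to .5.

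Downside: the pooled gate is less sensitive if the two programmes differ strongly. If only one works, with effect 0.80, the pooled difference is 0.40 and the gate has power Φ(0.40 / 0.158 − 1.960) = Φ(0.57) = .72 before clustering, against .99 for that arm's own contrast. The sponsor's assumption that the two programmes do equally well makes the pooled contrast the natural choice.

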### Randomization

After completion of baseline measures, patients are randomly allocated to one of the three groups using blocked cluster randomization. Patients are randomized in random blocks of 9 and 18 so that three consequent patients will always be distributed into the same treatment group. This strategy is used to obtain homogeneity in face-to-face treatment groups regarding number of days since the accident. The randomization list has been conducted in advance with a computer programme by a statistician and the therapist is blind for the upcoming blocks.

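### Allocation is by triples and Group 2 is treated in groups, yet neither the described mixed model nor the sample size names an allowance for clustering

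*Protocol article*

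**What the plan says.** The Randomization section of the protocol article states that "patients are randomly allocated to one of the three groups using blocked cluster randomization". Blocks are of 9 and 18, and "three consequent patients will always be distributed into the same treatment group". The reason given is: "This strategy is used to obtain homogeneity in face-to-face treatment groups regarding number of days since the accident". The triple is therefore the unit of allocation in all three arms.

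The arms then differ in how far patients share treatment:

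- **Group 2:** "Face-to-face intervention involves groups of three to six patients led by therapists", meeting seven times.
- **Group 1:** treated online with individual e-mail support, but questions and answers may be posted for others, "functioning as an additional support for the fellow patients, i.e. virtual group treatment". No group size is given.
- **Group 3:** no treatment beyond standard care, and no group sessions.

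Data management plans linear mixed models, partly to limit type I error, and says of them: "The Linear Mixed Models permit correlations (due to repeated measuring over time) between variables". It names no term for triple, block or therapy group.

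The sample-size section says "The power calculation is based on repeated three-group analysis" and "This gives a long-term effect size which is >.80". It arrives at 60 per group for power .90 at two-sided .05, with no ICC, cluster size or design effect.

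**The concern.** When whole triples are allocated together, the precision of an arm comparison depends on how alike the members of a triple are, not only on the number of patients. Here the triples are deliberately made alike in days since the accident. In Group 2 the patients then also share seven sessions, which can make their changes in Pain Disability Index alike. A model that handles only repeated measures within a patient captures neither source.

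At stake are the standard errors, confidence intervals and p-values of the primary comparisons. A model chosen partly to restrain type I error could then raise it. Contrasts involving Group 2 are the most exposed, and one of them, Internet against face-to-face delivery, is a stated aim of the trial.

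**Working it through.** **Inputs from the article.** Triples in all arms; blocks of 9 and 18; therapy groups of 3 to 6 in Group 2; 60 per group; two-sided .05; power .90; effect size above .80, taken here as a standardised difference of .80.

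**Input not in the article.** The ICC of the outcome being compared. I assume .01 to .20.

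**1. The plan's own figure.** For two independent groups, n = 2(1.960 + 1.282)²/0.80² ≈ 33 per group, not 60. With 60 per group and .80, power is .992. Power .90 with 60 per group corresponds to a difference of 3.242 × √(2/60) = 0.59. The article gives no SD or repeated-measures correlation, so its exact calculation cannot be recovered. Nothing shows that the surplus over 33 was meant for clustering.

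**2. Design effect, ignoring blocks.** DE = 1 + (m − 1) × ICC. The true SE is √DE times the naive SE. The true level of a nominal 5% test is 2[1 − Φ(1.96/√DE)]. For Group 2 in sixes against Group 3 in triples, the mean of the two design effects applies because the arms are equal in size. Power at .80 is Φ(.80/√(2·DE/60) − 1.96).

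| ICC | DE, triples | SE ratio | True level | Power at .80 | Mean DE, sixes v triples | True level | Power at .80 |
|---|---|---|---|---|---|---|---|
| .01 | 1.02 | 1.01 | 5.2% | .991 | 1.035 | 5.4% | .991 |
| .05 | 1.10 | 1.05 | 6.2% | .987 | 1.175 | 7.1% | .981 |
| .10 | 1.20 | 1.10 | 7.4% | .979 | 1.35 | 9.2% | .965 |
| .20 | 1.40 | 1.18 | 9.8% | .959 | 1.70 | 13.3% | .919 |

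With sixes in both compared arms, an extreme case, power at .80 is .975, .947 and .873 for ICC .05, .10 and .20. Only the last falls below .90.

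**3. Allowing for the blocks.** Each block holds the same number of triples per arm, so anything shared by a whole block cancels from an arm contrast. Let ρw be the correlation within a triple and ρb the correlation between triples of the same block. A triple mean without its block component has variance (ρw − ρb) + (1 − ρw)/3. Independence would give 1/3. The variance ratio is therefore 1 + 2ρw − 3ρb, and the naive test is too liberal only when ρb is below two thirds of ρw. Putting this ratio in place of DE:

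| ρw | ρb | Variance ratio | True level |
|---|---|---|---|
| .10 | 0 | 1.20 | 7.4% |
| .10 | .05 | 1.05 | 5.6% |
| .10 | .10 | 0.90 | 3.9% |
| .20 | .10 | 1.10 | 6.2% |

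A simulation of 20 blocks of 9 analysed with a plain t-test agrees with these to within about 0.2 percentage points. The levels in step 2 are the case ρb = 0, and so upper figures for a given within-cluster correlation.

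**The case against.** **Silence is not a decision.** A reader might infer that the plan has chosen to treat patients as independent. The article does not say so. Its sentence describes what mixed models permit and is not a list of random effects. A mixed model can carry a cluster term, and a fuller analysis plan may specify one. That stands, and it is why the conclusion is conditional on the model being run as described. But the article does state the correlation structure and names one source only, and its sample-size paragraph is silent on clustering although the same article specifies cluster allocation.

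**The triples are small and the blocks help.** Consecutive patients are not a natural cluster. In Group 3 the main visible source of likeness is time of arrival, which the blocks largely balance. This also stands: at ICC .01 the level is 5.2%, and with strong block correlation the naive test can be conservative. It is less reassuring for Group 2, where shared sessions after allocation create correlation that blocks cannot remove.

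**Power.** A reader might infer that the trial is underpowered. At the stated .80 it is not, except near sixes in both compared arms with ICC .20. A marked loss with triples (power .87 to .78 for ICC .05 to .20) appears only if the true effect is the 0.59 back-calculated in step 1, which the article does not claim.

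**Fairness between Groups 1 and 2.** A reader might also infer that ignoring clustering favours one of these arms. It does not. Their contrast has a single standard error, and understating it overstates certainty in either direction.

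**Conclusion.** The point holds in a conditional form. The article fixes cluster allocation and group treatment, but it describes a model and a sample size that name no allowance for either. If that description is followed, and correlation within triples or therapy groups exceeds what the blocks absorb, the between-arm standard errors are too small. The true level of a 5% test is then up to about 5.2% to 9.8% with triples (ICC .01 to .20) and about 7.1% to 13.3% for Group 2 in sixes against Group 3 in triples (ICC .05 to .20).

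These figures rest on an assumed ICC, on no correlation between triples of one block and, for the second range, on every Group 2 therapy group having six members. The actual inflation may be much smaller. The exposure is greatest for contrasts involving Group 2. The harm is to intervals and p-values, not mainly to power.

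**What to change.** **Data management.** Add, for example: *The model includes a random intercept for the cluster, defined as the randomised triple in Groups 1 and 3 and as the therapy group attended in Group 2, with a separate variance in Group 2. Randomisation block is included in the model. Degrees of freedom use the Satterthwaite or Kenward-Roger method.*

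One cluster level in Group 2 is enough. Where a therapy group is a single triple, the two levels coincide and cannot be told apart. With 60 patients there are only 10 to 20 therapy groups (60/6 to 60/3), which is also why small-sample degrees of freedom are needed.

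**Study size and power.** State the assumed ICC range and the power that remains at the stated effect size.

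**Data.** Record triple, block and therapy-group identifiers for each patient.

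**Cost.** The identifiers already arise from randomising and forming the groups, and nothing changes in treatment or recruitment. The price is slightly wider intervals and a slightly less favourable stated power.
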